## Abstract

**Introduction:**

Roux-en-Y gastric bypass and sleeve gastrectomy are the two most common bariatric surgery performed in the UK that result in comparable weight loss and remission of obesity-associated comorbidities. However, there is a paucity of studies examining the impact of these procedures on body composition, physical activity levels, sedentary behaviour, physical function and strength, dietary intake, health-related quality of life and costs.

**Methods and analysis:**

The BARI-LIFESTYLE observational study is a 1-year prospective, longitudinal cohort study within a real-world routine clinical care setting aiming to recruit 100 patients with severe obesity undergoing either primary Roux-en-Y gastric bypass or sleeve gastrectomy from two bariatric centres in London, UK. Participants will be followed up four times during the study period; presurgery baseline (T0) and at 3 (T1), 6 (T2) and 12 months (T3) postsurgery. In addition to the standard follow-up investigations, assessments including dual-energy X-ray absorptiometry scan, bioelectric impedance analysis, 6 min walk test, sit-to-stand test and handgrip test will be undertaken together with completion of questionnaires. Physical activity levels and sedentary behaviour will be assessed using accelerometer, and dietary intake will be recorded using a 3-day food diary. Outcome measures will include body weight, body fat mass, lean muscle mass, bone mineral density, physical activity levels, sedentary behaviour, physical function and strength, dietary intake, health-related quality of life, remission of comorbidities, healthcare resource utilisation and costs.

**Ethics and dissemination:**

This study has been reviewed and given a favourable ethical opinion by London-Dulwich Research Ethics Committee (17/LO/0950). The results will be presented to stakeholder groups locally, nationally and internationally and published in peer-reviewed medical journals. The lay-person summary of the findings will be published on the Centre for Obesity Research, University College London website (http://www.ucl.ac.uk/obesity).

Strengths and limitations of this studyA comprehensive prospective, longitudinal study with detailed assessments undertaken prior to and for 1 year following bariatric surgery examining changes in body composition, physical activity (PA) levels, sedentary behaviour, physical function and strength, dietary intake, health-related quality of life and costs, relative to baseline presurgery.The use of validated research tools (accelerometer to assess PA levels and sedentary behaviour, dual-energy X-ray absorptiometry (DXA) scan to assess body composition and validated questionnaires) will generate high-quality data.The study design does not include a conventional intensive lifestyle intervention (non-surgical) as a comparator group and patients will not be randomised to Roux-en-Y gastric bypass (RYGB) or sleeve gastrectomy (SG) in order to reflect current real-world clinical care.A potential sample selection bias due to exclusion of patients with functional limitation and/or non-ambulatory and patients with more than 200 kg of body weight owing to the weight limit of the DXA scan.A relatively small sample size, nevertheless, this number is adequate to generate indepth insights into the various outcomes of RYGB and SG as delivered in the UK healthcare setting.

## Introduction

Bariatric surgery engenders marked sustained weight loss and is recommended by the National Institute for Health and Care Excellence (NICE) as a treatment option for people of severe obesity,^1^ estimated to affect approximately 2.6 million adults in the UK.^2^ Roux-en-Y gastric bypass (RYGB) and sleeve gastrectomy (SG) are now the two most common procedures performed in the UK, which result in comparable weight loss and remission of obesity-associated comorbidities.^3^ However, there is a paucity of studies examining the impact of these procedures on body composition, particularly bone mineral density (BMD), physical activity (PA) levels, sedentary behaviour, physical function and strength, dietary intake, health-related quality of life (HRQoL) and costs. Furthermore, current eligibility and success criteria of bariatric surgery are mainly based on body weight, body mass index and excess weight loss but evidence have shown various beneficial outcomes of the surgery above and beyond weight loss alone, hence highlighting the need for more functional preoperative and postoperative patient assessment.^4 5^

Bariatric surgery leads to a marked decrease in fat mass (FM), but fat free mass (FFM) particularly bone mass is also reduced postsurgery,^6^ potentially negatively impacting on physical function and strength, and putting patients at increased risk of osteoporotic fracture in the future.^7 8^ Moreover, a recent study has revealed a positive association between changes in adiposity with cardiometabolic outcomes postsurgery, indicating the usefulness of incorporating body composition assessment.^9^ Surgical modification of the gastrointestinal tract impairs the intake and/or absorption of essential nutrients for bone health that consequently perturbs bone metabolism, leading to BMD deterioration.^7 8 10 11^ Significant bone mass loss has been reported to occur rapidly in the first year of surgery and continues to deteriorate up to 3 years even after maximum weight loss has been achieved.^10^ However, these data are mainly based on studies undertaken in patients who underwent RYGB whereas SG is now the most common procedure undertaken both in the UK and globally.^3 12^ Currently, it is unclear whether the rate of bone mass loss following SG parallels weight loss.^13–15^ Given that the number of younger patients and women of childbearing age undergoing bariatric surgery continues to increase and BMD measurement is not a routine follow-up investigation,^16^ there is an urgent need to assess the impact of RYGB and SG on bone health in the UK bariatric population.

Adherence to a postbariatric lifestyle changes is the cornerstone of a successful weight loss.^17^ Studies have shown that greater PA, lower sedentary time and high compliance to dietary recommendation postsurgery associate with greater weight loss and FM loss, preservation of lean muscle mass (LMM) and bone mass, as well as improvement in HRQoL.^18–22^ However, patients spend 80% of their waking time in sedentary behaviour postsurgery,^23^ activity that associates with increased risk of cardiometabolic disease and mortality.^24^ Following surgery, patients are advised to undertake at least 150 min of moderate-to-vigorous physical activity (MVPA) per week, a duration and intensity that are recommended to reap the metabolic benefit of PA.^25^ However, objectively measured MVPA decreases postsurgery with only 10% of patients achieving the recommended MVPA levels.^26^ Likewise, a recent study undertaken in the UK has reported that weight loss postsurgery did not correspond to improvement in MVPA and sedentary behaviour. However, the small sample size of this study (n=22) together with relatively short follow-up period limited its generalisability.^27^ Further studies are therefore required to expand the information in this regard. In terms of dietary recommendations, daily protein intake of 60 g or more postsurgery is crucial for increasing satiety, preserving LMM, improving body composition and preventing against weight regain.^28–31^ However, most patients are unable to achieve this in the first postoperative year, the period when rapid weight loss occurs.^32^ Whether this is also the case for UK bariatric population is not known as no such data has ever been reported thus far.^32^

Impaired HRQoL is common in obesity^33^ and often one of the driving factors for seeking weight loss surgery.^34^ HRQoL is defined as individuals’ perception of well-being that refers to physical, psychological and social domains of health.^35^ Most studies reported improvement in all HRQoL domains with greater scores observed in the first postoperative year although some studies showed that the improvement is limited to only the physical domain but not the mental health component of HRQoL.^36^ Despite mounting evidence in the international literature reporting the beneficial impact of bariatric surgery on HRQoL, data from the UK bariatric population does not exist.^37^ There is some evidence that bariatric surgery can reduce in cost savings that offset the initial costs of surgery, though little UK evidence for RYGB and SG.^38–40^

Taken together the lack of postoperative data coupled with recommendations from systematic reviews^26 32^ provide a strong rational to undertake a prospective study to evaluate the impact of RYGB and SG on body composition particularly BMD, PA levels, sedentary behaviour, physical function and strength, dietary intake, HRQoL and costs in a UK bariatric population. Information gained from this study will provide valuable data to inform the implementation of future postsurgery lifestyle programmes with the aim of maximising the beneficial outcomes of bariatric surgery as highlighted by NICE.^1^ This paper details the study design and outcomes of the BARI-LIFESTYLE observational study.

## Objectives

The overall objective of BARI-LIFESTYLE observational study is to evaluate the impact of RYGB and SG on changes in body weight, body composition, PA levels, sedentary behaviour, physical function and strength, dietary intake, HRQoL, remission of comorbidities, healthcare resource utilisation and costs in a cohort of 100 patients.

The specific objectives are to evaluate postsurgery changes in:percentage weight loss (%WL) at 1 year postsurgery, relative to baseline presurgery weight;body FM, assessed using dual-energy X-ray absorptiometry (DXA) scan and bioelectrical impedance analysis (BIA), relative to presurgery at 12 months postsurgery;LMM, assessed using DXA scan and BIA, relative to presurgery at 12 months postsurgery;BMD, assessed using DXA scan and BIA, relative to presurgery at 12 months postsurgery;PA levels (light, moderate, vigorous), percentage achieving 150 min of MVPA in a week and sedentary behaviour assessed using accelerometer at 3, 6 and 12 months postsurgery, relative to presurgery;physical function and strength assessed using 6 min walk test (6MWT), sit-to-stand (STS) test and handgrip test at 3, 6 and 12 months postsurgery, relative to presurgery;dietary intake assessed using food diary at 3, 6 and 12 months postsurgery, relative to presurgery;HRQoL assessed using EuroQol-5D-3L (EQ-5D-3L) and Impact of Weight on Quality of Life-Lite (IWQOL-Lite) at 3, 6 and 12 months postsurgery, relative to presurgery;characteristics of attitude and symptoms of depression assessed using Beck Depression Inventory-II (BDI-II) at 3, 6 and 12 months postsurgery, relative to presurgery;obesity-associated comorbidities (type 2 diabetes (T2D), dyslipidaemia, hypertension, obstructive sleep apnoea (OSA)) at 3, 6 and 12 months postsurgery, relative to presurgery;healthcare resource utilisation and costs assessed using an adapted version of the Client Service Receipt Inventory (CSRI) at 3, 6 and 12 months postsurgery, relative to presurgery.

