### Participants and recruitment

Patients will be screened for suitability for the study by the bariatric team at the study site and PIC based on the inclusion and exclusion criteria when they attend the standard presurgical assessment (box 1). Verbal consent will be sought from those fulfilling the eligibility criteria and interested in participating to be approached by a research investigator. Patients will be given a participant information sheet inviting them to participate in a 1-year prospective, longitudinal cohort study looking at the effect of bariatric surgery on body weight, body composition, PA levels, sedentary behaviour, physical function and strength, dietary intake, HRQoL, remission of comorbidities, healthcare resource utilisation and costs. Consented participants will then be scheduled to attend a baseline assessment, approximately 6 weeks before surgery day at the study site. Each participant will be given a Fitbit Alta HR to enable them to self-monitor their activity levels and to reduce sedentary behaviour. Based on the weekly number of bariatric procedures undertaken at UCLH and Whittington Hospital and after considering the eligibility criteria, estimated recruitment rate is approximately seven participants per month. Hence, the expected recruitment period for the study is 15–20 months.Box 1Participant eligibility criteria for participation in the BARI-LIFESTYLE observational studyInclusion criteriaAdult aged between 18 and 65 years.Planned to undergo either primary RYGB or SG surgery and fulfilling NICE eligibility criteria for bariatric surgery.^1^Able to read and write in English.Willing and able to provide written informed consent.Able to comply with study protocol.Willing and able to wear a Fitbit wrist-based activity tracker device and an ActiGraph device.Exclusion criteriaMore than 200 kg of body weight due to the limitation of DXA scan.Non-ambulatory.Functional limitation.DXA, dual-energy X-ray absorptiometry; NICE, National Institute for Health and Care Excellence; RYGB, Roux-en-Y gastric bypass; SG, sleeve gastrectomy.

All participants will receive the standardised postbariatric care as stipulated by NICE.^1^ Participants will attend the study site for monitoring of nutritional intake, vitamin and mineral deficiencies, comorbidities and medication review. Participants will receive verbal PA and dietary advice from a specialist nurse and dietitian at weeks 12 and 36 postsurgery, respectively.

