### Outcomes measures

Outcome measures will be collected at four study time points, designed to coincide with normal follow-up care visits; baseline visit at approximately 6 weeks before surgery (T0) then at 3 (T1), 6 (T2) and 12 months (T3) postsurgery (table 1).

**Table 1 T1:** Study timeline and investigations

	Baseline (T0)	Day of surgery	3 months postsurgery (T1)	6 months postsurgery (T2)	12 months postsurgery (T3)
Sociodemographic data	✓				
Height	✓				
Weight	✓	✓	✓	✓	✓
Blood pressure and heart rate	✓		✓	✓	✓
Dual-energy X-ray absorptiometry scan	✓				✓
Bioelectrical impedance analysis	✓		✓	✓	✓
Laboratory test	✓		✓	✓	✓
Physical activity levels (ActiGraph) and activity diary	✓		✓	✓	✓
Physical function and strength					
6 min walk test	✓		✓	✓	✓
Sit-to-stand	✓		✓	✓	✓
Handgrip test	✓		✓	✓	✓
Dietary intake (3-day food diary)	✓		✓	✓	✓
Completion of questionnaires					
EuroQol-5D-3L	✓		✓	✓	✓
Impact of weight on Quality of Life-Lite	✓		✓	✓	✓
Beck Depression Inventory-II	✓		✓	✓	✓
Client Service Receipt Inventory	✓		✓	✓	✓
Review of medication	✓		✓	✓	✓
Review of comorbidities	✓		✓	✓	✓

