#### PA levels and sedentary behaviour

PA and time spent in light, moderate and vigorous activities, and sedentary behaviour will be measured objectively using ActiGraph wGT3X-BT (Pensacola, Florida, USA), an accelerometer-based activity monitor.^45^ Participants will be instructed to wear the ActiGraph on their dominant hip for 1 week, from waking in the morning until going to bed at night, and to remove it only during water-based activities. Additionally, participants will be asked to keep an activity diary throughout the week, to assist interpretation of data from the device. Both the device and activity diary have to be returned to the investigators for data analysis (ActiLife software V.6.13.3; Pensacola, Florida, USA).

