#### Secondary outcomes analyses

Analyses of longitudinal secondary outcomes shall be performed using linear mixed effects regression models, with a normal distribution assumed for continuous outcomes (or a suitable transform of these outcomes). Model parameter estimates together with appropriate 95% CIs shall be reported. Categorical outcomes (eg, proportions of participants with comorbidities) shall be summarised in tabular form at each time point. Where appropriate (for example, for proportions), estimates and 95% CIs will be presented. To analyse costs, we will assume the costs measured at baseline for the preceding 6 months would persist during follow-up in the absence of surgery; we will then compare postsurgery costs with predicted costs that would have been incurred in the absence of surgery. To account for skewness of the cost data, we will use a generalised linear model with gamma family and log link.^58^

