## Advantage and limitation

This observational study will address the need for more high-quality data that examine the outcomes of RYGB and SG derived from the UK bariatric population. It will involve a comprehensive assessment and data collection at four study time points in the first year of surgery enabling an indepth analysis of changes in body composition, PA levels, sedentary behaviour, physical function and strength, dietary intake, HRQoL and costs, relative to presurgery. Data collection will be carried out by using validated assessment methods and questionnaires. Another advantage of this study is the use of DXA scan, a reference standard to measure body composition.^43^ Also, the use of accelerometer will generate high-quality data to measure objective PA levels and sedentary behaviour. Studies have shown that bariatric surgery patients tend to over-report their PA levels when assessed using the conventional PA questionnaires.^26^

This protocol for an observational study is not without limitations. First, the study design does not include a conventional intensive lifestyle intervention (non-surgical) as a comparator group. Second, patients will not be randomised for surgical procedure as this study does not aim to compare between RYGB and SG but aims to examine ‘real-world’ clinical outcomes where the patient/healthcare professional make an informed choice about which procedures is best. However, data that will be generated from this study will allow us to power a subsequent randomised study. Third, a potential sample selection bias due to the exclusion of patients with functional limitation (eg, cognitive impairment, walking difficulties) and/or non-ambulatory and patients with more than 200 kg of body weight owing to the weight limit of the DXA scan. Finally, given resource limitations, only approximately 100 patients will be recruited in this 1-year observational cohort study. Nevertheless, this sample size is adequate to generate indepth insights into the various outcomes of RYGB and SG.

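### Accelerometer changes at 3 and 6 months are confounded with season; a calendar term in the planned mixed models would remove most of this at almost no cost

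*Protocol article*

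**What the plan says.** All references are to the protocol article.

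- **Contrast.** Objectives lists light, moderate and vigorous activity, the share of participants reaching 150 min of MVPA a week, and "sedentary behaviour assessed using accelerometer at 3, 6 and 12 months postsurgery, relative to presurgery".
- **Schedule.** Outcomes measures sets the "baseline visit at approximately 6 weeks before surgery (T0) then at 3 (T1), 6 (T2) and 12 months (T3) postsurgery".
- **Measurement.** Under PA levels and sedentary behaviour, participants are to "wear the ActiGraph on their dominant hip for 1 week" at each time point, with an activity diary kept for the same week.
- **Comparator.** Advantage and limitation states that "the study design does not include a conventional intensive lifestyle intervention (non-surgical) as a comparator group".
- **Analysis.** Secondary outcomes analyses says "Analyses of longitudinal secondary outcomes shall be performed using linear mixed effects regression models". It names no covariates for the activity models. Categorical outcomes are to be tabulated at each visit, with intervals for proportions where appropriate.
- **Recruitment.** Two periods are given. Participants and recruitment expects about seven patients a month and says "the expected recruitment period for the study is 15–20 months". Study design and setting gives two years, 2018 to 2019, within a 36-month total from first enrolment to last follow-up.

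**The concern.** Each activity value belongs to one calendar week. If activity varies over the year, a change between two weeks that lie 4 to 7 months apart mixes the effect of surgery with the effect of season. A concurrent comparator would separate the two, but this design has none. A model of activity by visit with no calendar term assigns the whole change to time since surgery.

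Two things are at stake for the 3- and 6-month results. The first is a possible shift in the cohort mean, whose size depends on how recruitment is spread over the year. The second is extra variation in each participant's change, which widens the intervals however long recruitment lasts. The article wants these data to inform lifestyle programmes after surgery, so the early activity results will be used.

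**Working it through.** **Inputs from the article.** Baseline about 6 weeks before surgery; visits at 3, 6 and 12 months; 100 patients; about seven recruited a month; recruitment of 15 to 20 months or of 24 months; 36 months in total; up to 25% drop-out.

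**Assumption.** The article gives no seasonal pattern. I take a yearly cosine of amplitude A, where A is half the peak-to-trough swing. To illustrate, A is set at 10 to 20% of mean activity.

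**1. The plan's own figure.** The article has none for season. Its recruitment rate gives 100/7 = 14.3 months, just under the lower end of 15 to 20. An even 24 months would need only 100/24 = 4.2 patients a month.

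**2. Gap from baseline.** Six weeks is 42/30.44 = 1.38 months. The gaps are therefore 4.38, 7.38 and 13.38 months. At 30 degrees a month, the distance from baseline in the yearly cycle is 131, 221 (139 the short way round) and 41 degrees.

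**3. Largest seasonal part of one participant's change.** This is 2A|sin(π × gap/12)|; the root mean square over start dates is that value divided by √2.

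| Visit | Largest | Root mean square |
|---|---|---|
| 3 months | 1.82A | 1.29A |
| 6 months | 1.87A | 1.32A |
| 12 months | 0.71A | 0.50A |

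**4. What is left in the cohort mean.** Even recruitment over L months multiplies the largest contrast by |sin(πL/12)/(πL/12)|.

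| L (months) | Factor | 3 months | 6 months | 12 months |
|---|---|---|---|---|
| 14.3 | 0.151 | 0.28A | 0.28A | 0.11A |
| 15 | 0.180 | 0.33A | 0.34A | 0.13A |
| 17 | 0.217 | 0.40A | 0.41A | 0.15A |
| 18 | 0.212 | 0.39A | 0.40A | 0.15A |
| 20 | 0.165 | 0.30A | 0.31A | 0.12A |
| 22.6 | 0.060 | 0.11A | 0.11A | 0.04A |
| 24 | 0 | 0 | 0 | 0 |

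The 22.6-month row is the longest span of baseline visits that the 36-month total allows: 36 − 12 − 1.38 = 22.6.

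These are maxima over the calendar month in which recruitment starts. The bias can be near zero or of either sign. Over 15 to 20 months the factor of 0.165 to 0.217 means that about 78 to 83% of the contrast cancels.

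**5. Uneven recruitment.** If accrual rises linearly from zero, the largest bias at 3 and 6 months is 0.38A to 0.42A over 15 to 20 months, and 0.29A to 0.30A over 24 months.

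**6. Scale.** With A at 10 to 20% of mean activity, 0.30A to 0.41A is 3 to 8% of mean activity, and 0.11A is 1 to 2%. Against sampling error, take 100 × 0.75 = 75 completers (√75 = 8.66) and let A be 0.1 to 0.5 SD of the change score, also an assumption. The largest bias over 15 to 20 months then runs from 0.301 × 0.1 × 8.66 = 0.26 to 0.406 × 0.5 × 8.66 = 1.76 standard errors.

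**The case against.** **Two-year recruitment would remove the bias.** With even accrual over 24 months the mean bias is zero at every visit. A reader might infer from the 15 to 20 months alone that the seasons do not cancel. The article does not support that: it also states two years, and even over 15 to 20 months most of the contrast averages out. But the objection does not dispose of the point. The 36-month total leaves at most about 22.6 months for baseline visits, the stated recruitment rate implies 14.3, and exact cancellation needs even accrual. Seasonal noise in individual changes stays at any length.

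**The size is unknown.** This stands. The article gives no seasonal amplitude, so the importance of the bias cannot be fixed from it.

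**Season could decide the direction of the result.** A reader might infer this from the Introduction, which cites a UK study in which "weight loss postsurgery did not correspond to improvement in MVPA and sedentary behaviour". But the same paragraph also reports that objectively measured MVPA falls after surgery, and it discounts the UK study for its 22 patients and short follow-up. The article does not commit itself to expecting no change.

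**Covariates belong in the analysis plan.** This is fair. The article neither lists nor rules out covariates for the activity models, and a plan that is not shown may already contain a seasonal term. The absence of one here is therefore not an error. The point is a low-cost improvement to a contrast and schedule that the article does fix.

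**The 150-min share is only tabulated.** This also stands. Adjusting it would need a new binary longitudinal model, possibly with few achievers, so the main remedy should leave it alone.

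**Conclusion.** The point holds in a limited form. The 3- and 6-month activity changes are open to seasonal confounding, because each participant is compared with a week in a nearly opposite season, without a comparator and without a named calendar term. For an assumed yearly cosine, the bias in the cohort mean is at most about 0.3A to 0.4A under even recruitment over 15 to 20 months, about 0.11A over 22.6 months and zero over an even 24 months; uneven accrual can leave more. The start month may make it negligible. The 12-month contrast carries at most about 0.15A under even recruitment.

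A reader might take this as a threat to the study's main result. It is not: the primary outcome is percentage weight loss, and only the secondary accelerometer outcomes are concerned. The case for acting rests on the very low cost of the remedy, and on the gain in precision that does not depend on recruitment length. It does not rest on evidence that the bias is large.

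**What to change.** 1. In the linear mixed models for light, moderate, vigorous and sedentary time, add one sine and one cosine term of day of year for the recording week, or day length instead. Report the seasonally adjusted changes at 3, 6 and 12 months beside the unadjusted ones.
2. Keep the share reaching 150 min of MVPA as the planned table. A season-adjusted binary model can be an optional sensitivity analysis.
3. Reconcile the two recruitment periods (two years in Study design and setting; 15 to 20 months in Participants and recruitment) and report the calendar months of the baseline recordings.

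The cost is a sentence or two in the analysis plan and two parameters per model, set against up to four recorded weeks per participant. The recording dates should already be available from the device and the diary. No new visits or data are needed. If the full analysis plan already has such a term, only item 3 remains.
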